**Fig. 1 Fig1:**
[figure not shown]
Diagram of the stepped-wedge cluster randomized trial design. Participating hospitals are randomized to represented rows A to N and are divided in 7 blocks of 2 hospitals. T1–T8: time periods of 3 months. All patients will have a follow-up time of 12 months

**Fig. 2 Fig2:**
[figure not shown]
Individual patient pathway during participation in the PREPARATION study. ASA-PS, American Society of Anesthesiology Physical Status; MDT, multidisciplinary team [37]

### Recruitment

Consecutive high-risk noncardiac surgical patients will be assessed for potential eligibility at the preoperative assessment by the anesthesiologist and asked to participate if they fulfill the inclusion criteria. Eligible patients will receive written and video information about the study. Written informed consent will be obtained by a trained (research) nurse or a physician before surgery (control; phase 1) or before the MDT meeting (intervention; phase 2). To facilitate the inclusion of patients with limited health literacy in our study, we incorporated measures to guarantee that information about the study, questionnaires, and informed consent were written at a suitable language level (level B1).

Each hospital is estimated to include ten patients on average per 3 months. As hospitals vary in size and do not serve the same number of surgical patients, each hospital includes a different number of patients during each period of 3 months. Patients can withdraw consent at any time for any reason if they wish to do so. Data from patients who withdraw will be used in the analysis until the date of withdrawal, unless the patient states otherwise.

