European and US guidelines on perioperative care recommend preoperative multidisciplinary discussion for high-risk noncardiac surgical patients [15–17]. However, the added value of preoperative MDT discussions is currently based on the consensus of expert opinion, registries, and small or retrospective studies [5, 18, 19]. A previous study where high-risk patients planned for noncardiac surgery were selected for preoperative MDT discussions by the anesthesiologist at the preoperative clinic, showed that 43% of high-risk patients did not undergo surgery after discussion in a preoperative MDT meeting [5]. Cancelation of surgery was related to either the multidisciplinary team consensus-based advice or the patient’s own decision after reconsidering the surgical harm-benefit ratio.

The primary aim of this stepped-wedge cluster randomized trial (SW-CRT) is to assess whether preoperative MDT discussions for high-risk patients undergoing noncardiac surgery lead to a decrease in serious adverse events (SAEs) after 6 months. Secondly, the current trial will assess the cost-effectiveness of implementing a preoperative MDT meeting for high-risk noncardiac surgical patients compared to current preoperative screening practices. Furthermore, we aim to assess the effect of preoperative MDT discussions on survival, quality of life, and functional outcome, as well as the patient’s decision regret [20]. In addition, the quality of decision-making in these MDT meetings and facilitators and barriers for implementing MDT meetings in clinical practice will be investigated.

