### Study population

Anesthesiologists screen all patients scheduled for noncardiac surgery in the participating hospitals to identify those eligible for participation in this trial. Patients are eligible if they meet the following inclusion criteria: ≥ 18 years of ageAmerican Society of Anesthesiology (ASA) physical status score ≥ 3Clinical Frailty Scale ≥ 4 [22]Planned for elective or semi-elective non-cardiac surgeryAs stated by the 2010 Dutch preoperative guideline [23]:
∘ Doubt by the surgeon, anesthesiologist or patient regarding the harm-benefit ratio of the surgical procedure∘ Doubt if the correct measures were taken to limit the perioperative risk as much as possible∘ Doubt if the patient agrees with the surgical and anesthetic plan and the expected risks

The exclusion criteria are:No informed consentEmergency surgeryThe impossibility to communicate with the patient directly or through a third party, such as a relative or an interpreterProposed surgical procedure for which a preoperative MDT meeting, similar to the current study intervention, already exists in that hospital at the start of the study

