### Outcome

The primary outcome is the incidence of serious adverse events (SAEs) [25] at 6 months, defined as Grade 3 or more on the Clavien-Dindo classification following surgical intervention [26]. In the case of non-surgical management, serious adverse events will be graded accordingly, such as events necessitating endoscopic or surgical intervention, single or multiple organ failure, or death [26].

Secondary outcomes (Table 1) include:Cost-effectiveness from a societal and healthcare perspective, resource use measured by a patient cost questionnaire and via hospital electronic health records, health-related quality of life measured with the EQ-5D-5L for the construction of quality-adjusted life years (QALYs) [27] Functional status of the patient, measured by the 12-item WHO Disability Assessment Schedule 2.0 (WHODAS 2.0) [28]Patients’ experienced quality of life assessed by the abbreviated World Health Organization Quality of Life (WHOQOL BREF) [29]Patients’ regret about the treatment decision measured by the Decision Regret Scale [20]SurvivalThe attendance and self-assessed performance of MDT meetings are evaluated using a form that assesses various aspects such as structure, duration, cases reviewed, attending healthcare staff, medical specialty, initial queries, and treatment choices.Quality of MDT meetings by observations of multidisciplinary team discussion and decision-making by an independent, non-participant observer, using the MDT-MODe of decision-making (MDT-MODe) in a subset of MDT meetings [30, 31]Delay between preoperative screening, preoperative MDT meeting, and the surgical procedureFacilitators and barriers to organize preoperative MDT meetings

**Table 1 Tab1:** Primary and secondary outcomes, data sources, and used instrument/source of information

Outcome	Type of data source	Instrument/source
Serious adverse events	Registration	EHR
Functional status	Questionnaire	WHODAS 2.0 [28]
Health-related quality of life	Questionnaire	EQ-5D-5L} [27]
Quality of life	Questionnaire	WHOQOL BREF [29]
Decision regret	Questionnaire	Decision Regret Scale [20]
MDT characteristics	Registration	CRF
Perioperative management	Registration	CRF
MDT decision-making and facilitators and barriers	Observations and interviews	MDT-MODe [30]
Survival	Registration	EHR
Resource use	Questionnaire and registration	iMCQ and iPCQ: CRF: EHR [32]
Delay between preoperative screening, preoperative MDT, and surgery	Registration	CRF

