### Design

The PREPARATION study is designed as a stepped-wedge cluster randomized trial and will be executed in 14 hospitals without a currently established preoperative MDT meeting for high-risk noncardiac surgical patients [33]. The current trial employed a stepped-wedge design to address ethical concerns. This decision was based on the appreciation for existing MDT meetings among patients and physicians and the moral dilemma posed by denying patients the opportunity to have their cases discussed in preoperative MDT meetings in hospitals where such meetings are already standard practice [4, 5, 34–36]. Therefore, participating hospitals were selected based on the absence of established preoperative MDT meetings. At the start of the trial, each participating hospital performs preoperative screening and management as usual without preoperative MDT discussions (phase 1). At the crossover time points, two study centers switch from the control condition to the implementation of preoperative MDT discussions (phase 2). After 24 months, all hospitals have implemented a preoperative MDT meeting (i.e., all hospitals will be exposed to the intervention).

The design pattern matrix (Fig. 1) illustrates the trial design. In total, there will be 7 blocks, each consisting of two hospitals. Each hospital will be randomized to one of the seven sequences prior to the start of the study by an independent person from the coordinating center (Fig. 1). The individual patient flow, either as a patient in phase 1 (control) or as a patient in phase 2 (intervention), is shown in Fig. 2. Computer-generated lists of random numbers will be used to randomly assign the hospitals to one of the sequences (2 hospitals per sequence/block) for the 7 fixed number of points in time of crossover (steps). Furthermore, we will stratify on the size of the hospital (small versus large). This ensures that the control and intervention are balanced on the type and size of the hospital. Each hospital will be informed of its own crossover date 3 months prior to this time point to ensure ample time for preparing the implementation of the MDT. All patients will be individually followed in time until 1 year from the day of surgery or the day of the preoperative MDT meeting in case of nonsurgical management.

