### Statistical analysis plan

Primary outcome: Characteristics of the hospitals and patients will be summarized by group of randomization. Continuous variables will be described using means with standard deviations (SD) or medians with quartile ranges. We will check for imbalances between the control and intervention groups. Differences in continuous variables will be assessed using t-tests or non-parametric tests (Wilcoxon signed rank test) whichever is appropriate. Categorical variables will be described using numbers and percentages. Differences will be assessed using chi-square tests or Fisher’s exact tests. A *p*-value lower than 0.05 will be considered a statistically significant difference. We will determine the crude rate of SAEs for the control and intervention period. Data will be analyzed according to the intention to treat principle. Additionally, a per-protocol analysis will be performed based on whether the patients’ case was discussed in a preoperative MDT meeting or not. Differences in SAEs will be analyzed using a generalized linear mixed model (GLMM), with a random effect for hospital (accounting for the clustering), adjusted for the size of the hospital (used in the constrained randomization), and for the possible confounding effect of the calendar period. The result will be expressed as the risk difference and odds ratio with the appropriate 95% confidence intervals. In case there will be differences in prognostic variables in the control and intervention group, these potential confounding variables will be added to the GLMM model. Results for unadjusted (except for clustering effect, calendar time, and size of hospital) and adjusted (by potential confounding variables) will be reported. Secondary outcomes: Analyses of the secondary outcomes for categorical variables will also be performed using GLMM, in a similar model as the one used in the analysis of the primary outcome, with adjustment for other variables if indicated. In case of counts, such as the number of SAEs, GLMM will be used assuming a Poisson-dependent variable. These results will be reported as adjusted relative risk to summarize the difference between the control and intervention periods. For numeric outcome variables linear mixed models with adjustment for other variables will be used. The MDT meeting’s execution may be refined over time. Therefore, time-by-treatment effect interactions will also be analyzed. Subgroup analyses: The study will execute exploratory subgroup analyses based on factors such as age (< 70, ≥ 70 years), size of the hospital (small vs large), and intent of surgery (life-extending, functional, palliative, relief of pain or other complaints, other). Data analysis: Data analysis will be performed using the software package IBM SPSS Statistics, version 28 for Citrix (SPSS, Inc., Chicago, IL, USA) and R statistical language (https://www.r-project.org). All structured interviews will be audio recorded and transcribed verbatim. The transcripts will be analyzed by two independent coders, using thematic inductive analysis. Coders will meet on several occasions to compare their findings and differences will be discussed until consensus is reached.

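### Consent may be taken up to surgery in the control phase but only up to the MDT meeting in the intervention phase, and non-operated controls have no time zero, so selection can differ by phase

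*Protocol article*

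**What the plan says.** **Approach and consent.** Under Recruitment, consecutive patients in both phases are "assessed for potential eligibility at the preoperative assessment by the anesthesiologist and asked to participate if they fulfill the inclusion criteria". Written consent is then obtained "before surgery (control; phase 1) or before the MDT meeting (intervention; phase 2". Study population lists absence of informed consent as an exclusion criterion. One of its eligibility criteria is "Doubt by the surgeon, anesthesiologist or patient regarding the harm-benefit ratio of the surgical procedure".

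**Start of follow-up.** Under Design, each patient is followed for one year "from the day of surgery or the day of the preoperative MDT meeting in case of nonsurgical management". The article states no separate starting point for the 6-month primary outcome.

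**Outcome without surgery.** Under Outcome, "In the case of non-surgical management, serious adverse events will be graded accordingly", so patients who are not operated on contribute to the primary endpoint.

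**Analysis.** The statistical section states: "Data will be analyzed according to the intention to treat principle". The mixed model has a random hospital effect and adjusts for hospital size and calendar period. Prognostic variables that differ between the groups are added, and results are reported with and without them.

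**The concern.** The two consent limits sit on opposite sides of a decision that affects the outcome. The MDT meeting asks whether the operation should go ahead at all, and intervention patients must be in the trial before it is held. Control patients have no such meeting, but they were selected partly because someone doubted the operation, so some cancellation under usual care is plausible. A control patient who cancels, deteriorates or dies before signing is not in the trial. An intervention patient with the same course after the MDT is.

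The consent rule changes in each hospital at the moment the exposure changes. Any resulting difference in case mix is therefore carried by the treatment term, and neither the hospital effect nor the period effects can separate it out. What is at stake is whether the estimated difference in SAEs reflects the MDT or the way patients came to be counted.

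The start-of-follow-up rule compounds this. It has an entry for nonsurgical management, but that entry is the MDT date, which a control patient does not have.

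**Working it through.** **1. The rules side by side**

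| | Control phase | Intervention phase |
|---|---|---|
| Approach | preoperative assessment | preoperative assessment |
| Latest consent | surgery | MDT meeting |
| Where surgery is reconsidered, relative to that limit | before it (usual care) | after it (at or following the MDT) |
| Time zero if operated on | day of surgery | day of surgery |
| Time zero if not operated on | none stated | day of MDT meeting |

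The second, third and last rows differ by phase. The approach does not.

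**2. The plan's own figure**

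Inputs from Sample size, Recruitment and the Fig. 1 legend: 14 hospitals in 7 sequences, 8 periods, 10 patients per hospital-period, 43% versus 27.5%, ICC 0.1, cluster autocorrelation 0.8, two-sided 5%.

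- Patients: 14 × 8 × 10 = 1120, as stated.
- Generalised least squares on cluster-period means, with fixed period effects, nested-exchangeable correlation and the binary variance averaged over the two rates, gives a standard error of 0.0494.
- 0.155 / 0.0494 = 3.14. With 112 − 14 − 8 = 90 degrees of freedom, power is 87.4%, against 87% stated.

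The stated power reproduces under that reading of the correlation structure. It does not depend on when consent is taken, so it neither supports nor weakens the point.

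**3. Possible size of the selection effect (illustration)**

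Let x be the share of eligible controls lost before consent and q their SAE rate. The documents give neither. Assume that enrolled controls have the planned 43% rate and that the intervention phase has no comparable loss. Then:

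- rate in all eligible controls = (1 − x) × 0.43 + x × q
- overstatement of the control rate = 0.43 − that rate = x × (0.43 − q)

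| x | q = 10% | q = 20% |
|---|---|---|
| 5% | 0.05 × 0.33 = 1.65 points | 0.05 × 0.23 = 1.15 points |
| 10% | 3.3 points | 2.3 points |
| 20% | 6.6 points | 4.6 points |

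Against the 15.5-point target the extremes are 1.15 / 15.5 = 7% and 6.6 / 15.5 = 43%. The shift is zero at q = 43% and changes sign above it: x = 10% with q = 50% gives 0.10 × (0.43 − 0.50) = −0.7 points.

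**4. Consequence for the test (illustration)**

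Suppose the MDT has no effect, so that the intervention rate equals the rate in all eligible controls, and d = x × (0.43 − q) is spurious. The two-sided rejection probability is P(T > t₀.₉₇₅ − d/SE) + P(T < −t₀.₉₇₅ − d/SE). Here T has 12 degrees of freedom (14 hospitals − 2, a more cautious choice than in step 2) and SE is recomputed for the two rates.

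| x, q | Decay structure | Nested structure |
|---|---|---|
| 5%, 20% | 5.3% | 5.4% |
| 10%, 10% | 7.6% | 8.3% |
| 20%, 10% | 16.6% | 19.8% |

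The nominal level is 5%. At the low end the effect is negligible; at the high end it is not.

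**The case against.** The strongest reply is that the two limits are only outer bounds, each set at the next event in that pathway. Patients in both phases are identified and asked at the same visit, so consent may be equally early in practice. Intervention patients who drop out between the clinic and the MDT meeting are lost too. The patient pathway and the enrolment schedule are figures not available here, and either they or the full protocol may fix the consent point. The plan also checks for imbalance and adjusts for it.

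Most of this stands, and it rules out several stronger readings:

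- A reader might infer that cancelled controls never enter. The article does not say so; it only allows it. The issue is a possibly longer period for loss in the control phase, so x above is best read as the excess over the intervention phase.
- A reader might infer that the bias favours the MDT. That requires lost controls to have fewer SAEs than enrolled ones. Organ failure and death count as SAEs without surgery, so losing patients who deteriorate or die would work against the MDT.
- A reader might take the Introduction's figure, that "43% of high-risk patients did not undergo surgery after discussion in a preoperative MDT meeting", as a guide to the loss. It describes what happened after an MDT discussion. It says nothing about controls, and keeping such patients in the intervention group is correct under intention to treat.
- A reader might say that nothing downstream helps. Adjustment for measured prognostic variables helps in part.
- The rule that "Each hospital will be informed of its own crossover date 3 months prior to this time point" shows that hospitals know their phase, as is usual in an unblinded stepped wedge. It is not evidence about when consent is taken.

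The reply does not remove the stated difference between the limits, nor the absence of a start date for a non-operated control. Both are in the article's own wording.

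**Conclusion.** The point holds in a limited form. The written rules permit enrolment of non-operated patients to differ by phase. They also leave an enrolled, non-operated control without a time zero for an endpoint that is meant to include such patients. The resulting bias would be tied to exposure and only partly reachable by adjustment for measured imbalance.

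Size and direction cannot be determined from the documents. With assumed losses of 5–20% and SAE rates of 10–20% in those lost, against 43% in enrolled controls, the control rate would be overstated by about 1 to 7 points. Smaller differential loss, or a higher risk among those lost, would shrink or reverse this. The documents do not show that the bias has occurred. The case for change is that the rule leaves it possible and is cheap to close.

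**What to change.** 1. **One consent and registration landmark in both phases:** at the preoperative assessment, or within a fixed few days of it, and before any MDT meeting.
2. **One time zero for the primary outcome in both phases,** for example the date of preoperative assessment or of registration. The Trial status section gives a start of 1 November 2022, so recruitment had presumably begun when the article appeared. In that case add the common time zero at least as a sensitivity analysis.
3. **State that enrolled controls who are not operated on stay in the intention-to-treat analysis,** counted from that date.

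Cost: the consent window is slightly shorter and a few patients may be missed. Little new data is needed, because Table 1 already has the interval from preoperative screening recorded on the case report form and SAEs taken from the health record. With an earlier time zero, the 6-month window holds less postoperative time for patients whose surgery is later, which matters if the MDT delays surgery. Reporting the surgery-anchored result alongside it, and a longer window within the 12-month follow-up, would show whether this affects the conclusion. A consent change made part-way should take effect on one date in all hospitals. It cannot recover controls already lost before consent.

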### Statistical analysis plan

Primary outcome: Characteristics of the hospitals and patients will be summarized by group of randomization. Continuous variables will be described using means with standard deviations (SD) or medians with quartile ranges. We will check for imbalances between the control and intervention groups. Differences in continuous variables will be assessed using t-tests or non-parametric tests (Wilcoxon signed rank test) whichever is appropriate. Categorical variables will be described using numbers and percentages. Differences will be assessed using chi-square tests or Fisher’s exact tests. A *p*-value lower than 0.05 will be considered a statistically significant difference. We will determine the crude rate of SAEs for the control and intervention period. Data will be analyzed according to the intention to treat principle. Additionally, a per-protocol analysis will be performed based on whether the patients’ case was discussed in a preoperative MDT meeting or not. Differences in SAEs will be analyzed using a generalized linear mixed model (GLMM), with a random effect for hospital (accounting for the clustering), adjusted for the size of the hospital (used in the constrained randomization), and for the possible confounding effect of the calendar period. The result will be expressed as the risk difference and odds ratio with the appropriate 95% confidence intervals. In case there will be differences in prognostic variables in the control and intervention group, these potential confounding variables will be added to the GLMM model. Results for unadjusted (except for clustering effect, calendar time, and size of hospital) and adjusted (by potential confounding variables) will be reported. Secondary outcomes: Analyses of the secondary outcomes for categorical variables will also be performed using GLMM, in a similar model as the one used in the analysis of the primary outcome, with adjustment for other variables if indicated. In case of counts, such as the number of SAEs, GLMM will be used assuming a Poisson-dependent variable. These results will be reported as adjusted relative risk to summarize the difference between the control and intervention periods. For numeric outcome variables linear mixed models with adjustment for other variables will be used. The MDT meeting’s execution may be refined over time. Therefore, time-by-treatment effect interactions will also be analyzed. Subgroup analyses: The study will execute exploratory subgroup analyses based on factors such as age (< 70, ≥ 70 years), size of the hospital (small vs large), and intent of surgery (life-extending, functional, palliative, relief of pain or other complaints, other). Data analysis: Data analysis will be performed using the software package IBM SPSS Statistics, version 28 for Citrix (SPSS, Inc., Chicago, IL, USA) and R statistical language (https://www.r-project.org). All structured interviews will be audio recorded and transcribed verbatim. The transcripts will be analyzed by two independent coders, using thematic inductive analysis. Coders will meet on several occasions to compare their findings and differences will be discussed until consensus is reached.

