
### Sample size

Statistical analysis determined that a sample size of 14 clusters, or around 1120 patients, would be needed to identify a 15.5% decrease in clinically significant SAEs (Clavien-Dindo ≥ 3). The results showed that this sample size would achieve 87% power with a two-sided test at a 5% significance level. These calculations were based on pilot data that showed a 43% adverse event rate in the control group and a 27.5% rate in the intervention group [5]. We used the Shiny CRT calculator: https://clusterrcts.shinyapps.io/rshinyapp to calculate the sample [38]. No literature is available to guide potential values of the period intra-cluster coefficient (ICC). We assumed that the outcomes of different patients from the same hospital would not change over different periods, apart from the difference in the control condition period and the MDT meeting period. However, we chose a non-exchangeable correlation structure (with a two-period decay) in our sample size calculation to consider an unexpected decline. For the ICC, we used a moderate value of 0.1, and for the cluster auto-correlation (CACs), a value of 0.8. Lower values of the ICC lead to a higher power. Furthermore, we used the T-distribution as we have relatively small samples. We expect an average of 20 new high-risk noncardiac patients in each block. We assume that no correlation exists between hospitals. As we expect patients to drop out we will include 1200 patients in this study (± 7% dropout = 1120).

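### The primary GLMM has only a hospital random effect, so the planned safeguard against falling within-hospital correlation (CAC 0.8) protects power but not the test

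*Protocol article*

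**What the plan says.** Protocol article, Statistical analysis plan: "Differences in SAEs will be analyzed using a generalized linear mixed model (GLMM), with a random effect for hospital (accounting for the clustering"). The fixed part adjusts for hospital size and "for the possible confounding effect of the calendar period". No other random effect is named. Categorical secondary outcomes get a similar model, counts a Poisson GLMM and numeric outcomes a linear mixed model.

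Protocol article, Sample size: the authors assumed that "outcomes of different patients from the same hospital would not change over different periods", apart from the change from control to intervention. They then wrote: "we chose a non-exchangeable correlation structure (with a two-period decay) in our sample size calculation to consider an unexpected decline". The values were: "For the ICC, we used a moderate value of 0.1, and for the cluster auto-correlation (CACs), a value of 0.8". On the reference distribution: "Furthermore, we used the T-distribution as we have relatively small samples". No degrees of freedom are given. The result was that "this sample size would achieve 87% power with a two-sided test at a 5% significance level".

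**The concern.** In a stepped wedge, much of the information on treatment comes from comparing each hospital with itself before and after its crossover. If hospitals also drift from quarter to quarter in their own way, that drift is noise in exactly this comparison. A fixed calendar-period effect removes only the movement that all hospitals share. A lone hospital intercept has no term for hospital-specific movement, so it treats such movement as patient-level noise that averages out, and reports too small a standard error.

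The sample size calculation allows for this drift and the analysis model does not. This is not a detail left to another document, because the article states the random part of the model. At stake are the p-value and confidence interval of the primary comparison, and those of any secondary outcome given the same random part.

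**Working it through.** **Inputs.** 14 hospitals, 7 sequences of 2 (Design); 8 periods of 3 months (legend of Fig. 1); 10 patients per hospital per period (Recruitment), so 14 × 8 × 10 = 1120; rates 43% and 27.5%, difference 0.155; ICC 0.1; CAC 0.8; two-sided 5% (Sample size).

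**Step 1: reproduce the 87%.** I used the generalised least squares variance of the treatment effect on hospital-period means, with fixed period effects and binomial variance at the mean rate: 0.3525 × 0.6475 = 0.2282. Power is the probability that a z or t variable falls below 0.155/SE minus the critical value.

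| Correlation | SE | z | t, 103 df | t, 90 df | t, 12 df |
|---|---|---|---|---|---|
| One lower value for all other periods (block-exchangeable), CAC 0.8 | 0.0500 | 87.2% | 86.6% | 86.5% | 81.1–81.2% |
| Discrete-time decay, 0.8 per period | 0.0559 | 79% | 78% | 78% | 72% |
| Exchangeable, CAC 1 | 0.0460 | 92% | 92% | 91% | 87% |

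Here 103 = 112 hospital-periods − 9 fixed effects, 90 = 103 − 13 for hospitals, and 12 = 14 − 2. The stated structure gives the stated power in its block-exchangeable form with large degrees of freedom. Exchangeable correlation with 12 df also gives 87%, but the text says that the structure was not exchangeable.

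**Step 2: why the standard error is understated.** On a scale where one patient has variance 1, a hospital-period mean varies around its own hospital with variance

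- true: ICC × (1 − CAC) + (1 − ICC)/10 = 0.02 + 0.09 = 0.11
- as the hospital-only model sees it: (1 − ICC × CAC)/10 = 0.92/10 = 0.092

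SE ratio ≈ √(0.092/0.11) = 0.91. The full calculation (the limit of the restricted-likelihood fit of the hospital-only model, its model SE set against the true SE) gives 0.0461/0.0501 = 0.92, about 8% too small.

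**Step 3: type I error.** With a z test this is 2 × Φ(−1.96 × 0.92) = 2 × Φ(−1.80) ≈ 7.2%. Two simulations of the logistic GLMM under the null at 43% gave 7.9% and 8.7%. Hence about 7–9%.

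**Step 4: range** (full calculation, z test).

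| ICC | CAC | Structure | SE ratio | Type I error |
|---|---|---|---|---|
| 0.1 | 1 | exchangeable | 1.00 | 5.0% |
| 0.1 | 0.95 | block | 0.98 | 5.5% |
| 0.1 | 0.8 | block | 0.92 | 7.2% |
| 0.1 | 0.6 | block | 0.86 | 9.2% |
| 0.05 | 0.8 | block | 0.96 | 6.0% |
| 0.02 | 0.8 | block | 0.99 | 5.3% |
| 0.1 | 0.8 | decay | 0.79 | 12.2% |

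ICC values other than 0.1 and CAC values other than 0.8 and 1 are assumptions made to show the range.

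**Step 5: after adding a hospital-by-period effect.** With block-exchangeable data at CAC 0.8, simulated type I error was 5.8% (z) or 5.4% (t, 90 df) in 294 fits, with a Monte Carlo error of about 1.3 points.

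**Limits.** The calculation and simulations take equal hospital-period sizes. One simulation omitted the hospital-size covariate and lost 2–9% of fits to numerical failure. The closed-form results agree in direction and size.

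**The case against.** The best defence is the document's own sentence that no change over periods is expected. On that view CAC 0.8 is a cautious value for power, and the hospital-only model matches the stated belief. This stands in part: a reader might infer that the standard error will be too small and the type I error above 5% whatever happens, and the document does not support that. It depends on a CAC below 1 and shrinks with the ICC, for which the authors say no literature gives guidance. But a safeguard taken seriously enough to size the trial should also protect the test, and at present it does not.

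Three stronger readings are also unsupported.

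- **The missing small-sample correction inflates the error by itself.** The Statistical analysis plan section names no reference distribution. The z test is an assumption made here, and an article may leave this to a fuller document. The size at CAC 1 is not settled either: one simulation gave 6.9% and another 5.1%.
- **The error is about 12%.** Discrete-time decay gives 12–13%, but it yields 78–79% power with z or large degrees of freedom, so it does not fit the stated 87%.
- **Most of the inflation is bound to appear.** A t test on 12 df would bring the block-exchangeable case to about 4.5% by calculation, or 5.0% and 6.1% in the two simulations. It would leave 8–9% under decay. However, it would lower the power of the planned design to about 81%, so it is not a free substitute for the missing term.

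**Conclusion.** The point holds as a conditional inconsistency. The random part of the primary model implies CAC 1, while the sample size rests on CAC 0.8. If ICC 0.1 and CAC 0.8 are true and the structure is block-exchangeable, the model SE is about 8% too small and type I error about 7–9% with a Wald z test. It is nominal at CAC 1 and about 5–6% at ICC 0.02–0.05. The larger figure of 12–13% needs exponential decay and should not be the headline. The mismatch deserves correction because it affects the primary test and costs little to remove. It does not show that the trial's test is invalid under the expectation that the authors state.

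**What to change.** 1. Add a random hospital-by-period effect to the primary GLMM, and use the same random part in the similar models for secondary outcomes.
2. Keep the hospital-only model as a sensitivity analysis, and add one with discrete-time decay.
3. State the degrees of freedom behind the t-distribution in the sample size, and use the same reference for the primary test and interval.
4. Say which structure the two-period decay means, so that design and analysis can be matched.

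Cost: a few lines of wording and code, settled before outcome data by study condition are seen. The design SE rises from about 0.046 to 0.050, so intervals are about 8–9% wider than the hospital-only model would report. No extra patients are needed to keep the stated power, since the 87% already assumes this structure with z or large degrees of freedom. If about 12 degrees of freedom are chosen, power is about 81% and the stated figure should be revised.
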